### 2.11. Data Analysis

The intent-to-treat (ITT) sample comprises all randomized participants. Univariate descriptive statistics and frequency distributions will be calculated for clinical and other baseline covariates for the total sample to describe the study population, and by intervention group to assess the similarity of the treatment arms at baseline to confirm randomization success and to identify potential confounding variables to be used as covariates in secondary analyses. We will use a longitudinal general linear model approach as the analytic framework for inferential analyses. This method allows for missing data under the assumption of missing at random (MAR), accounts for the correlated longitudinal measurements within subjects, and accommodates a wide range of distributional assumptions through the specification of appropriate link functions. For the primary analyses of patient clinical outcomes (HbA1C, blood pressure, and lipid levels) and patient-reported outcomes, the identify link function will be used to compare 6 month treatment means and longitudinal trajectories for the DM Social Needs and usual care arms. Each outcome within each domain will be used separately as the dependent variable in the models with intervention, time, and time-by-intervention as the primary independent variables and baseline score for a given outcome variable as an adjustment covariable. In further secondary analyses, covariates (e.g., sociodemographics, health literacy, and comorbidities) will be added to each model to adjust for confounding variables, if indicated. Model-generated least squares intervention means, and the intervention mean difference (effect size), for clinical and patient-reported outcomes will be estimated, and intervention differences will be compared for significance at the primary endpoint (6 month) using 90% confidence intervals and *p*-values for appropriate model-derived contrasts. 

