### Study Aims and Objectives

The primary aim of this study is to test the preliminary efficacy of the DM Social Needs intervention on clinical outcomes (HbA1C, blood pressure, and LDL levels) in older AAs with uncontrolled T2DM. The secondary aim is to test the preliminary efficacy of the DM Social Needs intervention on patient-reported outcomes (based on PROMIS measures) in older AAs with uncontrolled T2DM. The primary outcome is HbA1C at 6 months post randomization, the secondary outcome is blood pressure at 6 months post randomization, and the tertiary outcomes are LDL and patient-reported outcomes of global health, fatigue, pain interference, and social participation at 6 months post randomization. 

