### 2.3. Trial Population and Recruitment

A total of 100 AAs aged 50 and older with poorly controlled T2DM (HbA1C ≥ 8%) will be randomized in a 1:1 ratio into one of two study groups—(1) nurse-led, telephone-delivered DM Social Needs intervention that includes education and skills training on diabetes management and problem solving and the resolution of social needs during monthly, 60 minute phone calls (*n* = 50); and (2) an enhanced usual care group that will receive mailed diabetes education materials each month for 6 months in accordance with recommendations from the ADA (*n* = 50). Participants will be followed for 6 months to evaluate the preliminary efficacy of the intervention on clinical outcomes (HbA1C, blood pressure, and LDL levels) and patient-reported outcomes (PROs).

A multifaceted approach will be used to recruit AA older adults with poorly controlled T2DM after receiving approval from the Institutional Review Board (IRB). (1) Housing Authorities. The study PI will meet with housing authority leadership for public and senior housing communities to obtain approval to recruit and share information about the study at their locations. (2) Community Leaders. The study PI will meet with other community leaders including church/religious leaders, small business owners, and federally qualified health center and community center leaders to obtain approval to recruit and share information about the study at their locations. (3) Mailing Lists. Targeted mailing lists obtained from electronic health records and other publicly available sources will be used to send letters describing the study and providing instructions on how to contact the research team will be sent to older African Americans in an effort to reach eligible patients. (4) Referrals. Referrals will be accepted from healthcare providers, community members, or other study participants. Individuals who are referred to participate will be contacted by the research team to assess interest, willingness, and eligibility to participate.

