### 2.4. Randomization

A permuted block randomization method will be used to assign patients to control or intervention. Block size will be varied to minimize the likelihood that the blind will be broken. The randomization will be computer generated and stratified by screening HbA1C levels (8–10% vs. >10%). Study staff responsible for completing surveys and collecting measures at baseline, 3 months, and 6 months post randomization will be blinded to study group assignment. 

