### 2.8. Primary Outcomes

The three primary outcomes for this study are HbA1C, blood pressure, and low-density lipoprotein cholesterol levels. Primary outcomes will be collected at baseline, 3 months, and 6 months post randomization. 

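### Blood pressure, LDL and PROMIS models leave out the HbA1C randomization stratum; if the stratum is prognostic, their standard errors are slightly too large (minor, easily fixed)

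*Protocol article*

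**What the plan says.** **Design.** Section 2.4 states: "A permuted block randomization method will be used to assign patients to control or intervention". Block sizes vary, and the list is "computer generated and stratified by screening HbA1C levels", with two strata: 8–10% and above 10%. Under Section 2.3, participants "will be randomized in a 1:1 ratio into one of two study groups".

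**Analysis.** Section 2.11 sets out one longitudinal model form for all clinical and patient-reported outcomes, each outcome analysed separately in "models with intervention, time, and time-by-intervention as the primary independent variables and baseline score for a given outcome variable as an adjustment covariable". Further covariates are left to later work: "In further secondary analyses, covariates (e.g., sociodemographics, health literacy, and comorbidities) will be added to each model to adjust for confounding variables, if indicated". The stratum appears neither among the model terms nor among those examples.

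**Rank of the outcomes.** Study Aims and Objectives says: "The primary outcome is HbA1C at 6 months post randomization", with blood pressure secondary, and LDL and the patient-reported outcomes tertiary. Section 2.8 says: "The three primary outcomes for this study are HbA1C, blood pressure, and low-density lipoprotein cholesterol levels". Section 2.11 treats all of them as primary analyses under the same model.

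**The concern.** Blocking within strata makes the two arms nearly equal in their mix of lower and higher screening HbA1C. Any outcome difference between strata then contributes almost nothing to the error of the treatment comparison. A model without the stratum does not know this. It leaves the between-stratum variation in the residual, so the standard error it reports exceeds the real variability of the estimate.

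For HbA1C the outcome's own baseline stands in for the stratum. For blood pressure, LDL and the PROMIS scales the stated models have nothing that does so.

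What is at stake is the accuracy of the reported intervals and p-values. Section 2.11 judges arm differences at 6 months by 90% confidence intervals and p-values, Section 2.10 presents interval width as a planned product, and the Discussion says the preliminary results will support a proposal for a larger trial. Section 2.10 also relaxes alpha to 0.10 because this is a pilot, and a test that runs below its nominal level works against that choice.

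**Working it through.** No figure in the plan depends on the stratum, so there is none to reproduce for this point. The figures in Section 2.10 are used only to set the scale.

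**Inputs from the article**
- Two-sided alpha 0.10 (critical value 1.645), 40 per arm, effect 0.3 sd, within-participant correlation up to 0.5, 90% half-width ±0.26 sd, SD 19.9 mmHg for systolic blood pressure (Section 2.10).
- 1:1 allocation, permuted blocks of varying size, two HbA1C strata (Sections 2.3 and 2.4).

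**Assumed, because the article gives no figure**
- R², the share of outcome variance explained by the stratum after own-baseline adjustment: 0.01 to 0.10.
- For the simulation: 40% of patients above 10%, own-baseline correlation 0.5, block sizes 2, 4 and 6, a single 6-month baseline-adjusted comparison, and complete data on 80 patients.

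**Step 1: closed form.** Let V be the residual variance after own-baseline adjustment. With balance on the stratum, the estimator's true variance is close to (1 − R²)·V·2/n, whether or not the stratum is in the model. The model without it reports V·2/n. Hence:
- reported SE / true SE = 1/√(1 − R²)
- actual alpha = 2·[1 − Φ(1.645/√(1 − R²))]

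Taking the plan's ±0.26 sd as the half-width without the stratum, the half-width with it is 0.26·√(1 − R²). In systolic blood pressure, ±0.26 sd is 0.26 × 19.9 = ±5.17 mmHg.

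| R² | SE ratio | Actual alpha | Half-width with stratum (sd) | Systolic BP (mmHg) |
|---|---|---|---|---|
| 0.01 | 1.005 | 0.098 | 0.259 | 5.15 |
| 0.02 | 1.010 | 0.097 | 0.257 | 5.12 |
| 0.05 | 1.026 | 0.092 | 0.253 | 5.04 |
| 0.10 | 1.054 | 0.083 | 0.247 | 4.91 |

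**Step 2: simulation.** For each R² and each effect size (none, and 0.3 sd), 10,000 stratified permuted-block trials were generated, and each was fitted without and with the stratum. Each cell shows without / with. The SE and SD columns come from the no-effect runs.

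| R² | Type I error | Mean reported SE | SD of estimate | Power at 0.3 sd |
|---|---|---|---|---|
| 0 | 0.100 / 0.100 | 0.194 / 0.194 | 0.195 / 0.195 | 45.4% / 45.4% |
| 0.01 | 0.096 / 0.096 | 0.194 / 0.193 | 0.193 / 0.193 | 45.8% / 46.1% |
| 0.05 | 0.0945 / 0.103 | 0.194 / 0.189 | 0.1913 / 0.1911 | 46.1% / 47.5% |
| 0.10 | 0.085 / 0.102 | 0.194 / 0.184 | 0.1865 / 0.1860 | 44.8% / 48.2% |

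The Monte Carlo error of a type I rate here is √(0.1 × 0.9/10,000) = 0.003, so the R² = 0.01 row cannot be told apart from no effect. The power differences, from unrounded values, are 0.3, 1.5 and 3.4 points. The SD of the estimate is nearly the same in both fits; it is the reported SE that differs.

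**Step 3: HbA1C.** With continuous baseline HbA1C in the model, adding the stratum changed nothing material: type I error 0.102 without and 0.101 with, power 45.4% and 45.2%.

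**Note on the power level.** For a 6-month baseline-adjusted comparison at correlation 0.5, 40 per arm gives Φ(0.3/√(0.75 × 2/40) − 1.645) = Φ(1.549 − 1.645) ≈ 46%, which agrees with the simulation. That this is not the 80% claimed in Section 2.10 is a separate matter that does not arise from the stratum. Only the differences between the two fits are used here.

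**The case against.** The strongest reply has four parts.

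1. **The outcome named first in the aims is untouched.** This stands, provided the baseline HbA1C in the model is the screening value or close to it. Under the ranking in Study Aims and Objectives, the point reaches only secondary and tertiary outcomes. Section 2.8 instead calls blood pressure and LDL primary, so the weight of the point depends on a contradiction that the article leaves open.
2. **The harm is conditional.** This also stands. Own baseline is already in each model, and the article offers nothing on whether an HbA1C split at 10% adds to it for blood pressure, LDL or PROMIS scores. If it adds nothing, omitting it costs nothing.
3. **The error is on the safe side.** This stands too. A reader might infer from a mismatch between design and analysis that the tests are invalid or the estimates biased. The calculation shows the reverse: the tests are conservative, and the omission brings no bias. A reader might also infer that the trial throws away precision worth several patients. That is not supported, because blocking has already secured nearly all of the true gain. What is lost is reported precision and a little power.
4. **The article condenses a fuller plan.** This carries some weight: the secondary covariate list is open-ended, and an unseen analysis plan may include the stratum. But Section 2.11 is not silent. It names the model terms down to the baseline covariable, and the stratum is not there. If a fuller document includes it, the two texts should be aligned.

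**Conclusion.** The point holds as a minor one. The models stated for blood pressure, LDL and the PROMIS outcomes omit the factor on which randomization was stratified, and nothing else in them carries it.

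If the stratum is prognostic beyond own baseline, with partial R² between 0.01 and 0.10, reported standard errors are too large by about 0.5% to 5% and the 90% intervals are too wide in proportion. For systolic blood pressure that is at most about a quarter of a mmHg on each side (5.17 against 4.91). The nominal 10% test runs at about 9.8% to 8.3%, and power falls by roughly 0.3 to 3.4 points.

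Confidence is high on the omission and on the direction of its effect. The size rests wholly on the assumed R² range and, for the simulated figures, on the simulation settings listed above. The documents do not support a claim of inflated type I error, of a biased estimate, of a material loss in true precision, or of any real effect on the HbA1C analysis.

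**What to change.** In Section 2.11, and in the analysis plan if it reads the same way, add the randomization stratum (8–10% against above 10%) as a fixed effect in the blood pressure, LDL and PROMIS models. Continuous screening HbA1C would serve equally well. Adding the stratum to the HbA1C model, alongside continuous baseline HbA1C, is optional and only for consistency.

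The cost is one model term and one degree of freedom. The variable is already recorded, because it was needed to randomize. The article reports 53 of 100 participants randomized and defers analysis until all follow-up is complete, so on that timetable the term can be fixed in advance.

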## 3. Results

The study team has recruited 53 out of 100 participants to date, and is on track to complete the study prior to the end of the funding period. Data analyses will be conducted following the completion of enrollment and follow-up visits for all 100 participants. The results from this study will include the final number of total study participants along with the number of participants assigned to the DM Social Needs intervention and enhanced usual care groups. Additionally, a CONSORT diagram will be used to show the flow of patients through the study. Baseline characteristics for demographics for the ITT sample will be presented by study group. Within- and between-group changes in the three primary outcomes of HbA1C, blood pressure, and LDL levels from baseline to the 6 month primary endpoint will also be reported.

## 4. Discussion

This novel study will not only offer diabetes education and skills training to an older adult African American population with a high risk of poor diabetes-related outcomes, but it will also offer insights into understanding the impact of going beyond social needs referral and navigation to social needs resolution on clinical and self-reported outcomes. If it is established that resolving social needs and diabetes education and skills training are important in diabetes control; future studies will be planned to implement the DM Social Needs intervention at a population level, and efforts will be made to inform policy change to facilitate payors to use scalable efforts to improve outcomes for older African Americans with diabetes.

A number of strategies will be employed to address potential pitfalls and any high-risk aspects of the proposed work. First, potential pitfalls exist regarding the completion of the study, including recruitment and retention. The recruitment of 100 participants meeting the inclusion and exclusion criteria is not expected to pose a concern based on prior methods developed and used by the research team. The study team has successfully enrolled 53 participants to date and is on target to complete enrollment according to the planned timeline. Based on previous discussions with community partners, improving diabetes outcomes for older adults is a topic of concern and African American communities are interested in participating in studies to address this problem. While the retention of participants is of concern, strategies known to be effective based on prior R01 studies conducted by collaborators ([name], [name], and [name]) will be used. These strategies include providing appointment cards for follow-up visits, sending appointment reminders, and offering incentives at visits to compensate for inconvenience and time. Similarly, the research team has existing strategies in place for delivering the intervention without contamination, and ensuring fidelity to the protocol. Prior to initiating any study procedures, a protocol training will be held with the research team including research assistants and health educators that includes detailed discussion of the rationale for the study and the intervention. 

The anticipated duration of the study is three years. In the first quarter of Year 1, we will finalize the clinical trial protocol and register the study on clinicaltrials.gov, finalize consent forms and obtain IRB approval, develop standard operating procedures, and train study staff. We will randomize 30 patients by the end of Year 1 (30%), 70 patients by the end of Year 2 (70%), and 100 patients by Quarter 2 of Year 3 (100%); with an average of 4 patients enrolled per month. Each patient will be followed for 6 months with study visits at baseline, 3 months, and 6 months post randomization. The intervention will be delivered monthly for 6 months, and follow-up will take place during years 1–3. The completion of this project will provide preliminary data for an adequately powered problem solving and social needs resolution intervention by Year 3 of the award. This study will pave the way for the optimization of care delivery among older AAs with T2DM and social needs, thereby reducing complications, improving quality of life for older AAs with poorly controlled T2DM (Table 3). 

Study limitations include a relatively small sample size, as is the norm for pilot studies. Preliminary results generated after completing the study will be used to submit an NIH R01 proposal for a larger study that will be powered to assess the efficacy of the intervention on diabetes-related outcomes. In addition, by enrolling only African American adults aged 50 and older, study findings will not be generalizable to the general older adult population. 

## 5. Conclusions

Overall, the results from this study will provide insights into the efficacy of a combined diabetes education and skills training and social needs resolution intervention for older African Americans with poorly controlled type 2 diabetes and inform strategies to improve diabetes outcomes for this vulnerable population.

## Figures and Tables

**Figure 1 healthcare-12-01991-f001:**
[figure not shown]
Flow diagram of study design.

**Table 1 healthcare-12-01991-t001:** Data collection schedule.

Measures	Assessment		
	Baseline	3 Months	6 Months
Primary Outcomes			
Hemoglobin A1C	x	x	x
Blood pressure	x	x	x
Low-density lipoprotein cholesterol	x	x	x
Secondary Outcomes (PROMIS Measures)			
Global health	x	x	x
Fatigue	x	x	x
Pain	x	x	x
Social participation	x	x	x
Process and Mediators/Moderators			
Accountable Health Communities’ Health-Related Social Needs (i.e., housing instability, food insecurity, and transportation)	x	x	x
Summary of Diabetes Self-Care Activities (SDSCAs)	x	x	x
Medication adherence	x	x	x
Diabetes knowledge	x	x	x
Depression	x	x	x
Anxiety	x	x	x
Covariates			
Sociodemographics	x	x	x
Health literacy	x	x	x
Comorbidities	x	x	x

**Table 2 healthcare-12-01991-t002:** Description of the measures and scales used to collect data.

Variable	Method Measured
Primary Outcomes	
Hemoglobin A1C	Blood will be collected and analyzed at baseline, 3 months, and 6 months.
Blood pressure	Blood pressure readings will be obtained using automated blood pressure monitors (OMRON IntelliSenseTM HEM-907XL, Dalian, China). Three readings will be collected and the average will be documented as the participant’s blood pressure.
LDL cholesterol	Blood will be collected and analyzed at baseline, 3 months, and 6 months.
Secondary Outcomes	
Global health	The global health PROMIS measure is a 10-item questionnaire to measure overall physical and mental health [37].
Fatigue	The short form 8a PROMIS measure is an 8-item questionnaire to assess how fatigued an individual felt during the last 7 days [38].
Pain interference	The 8-item pain interference PROMIS measure assesses how much pain interfered with activities during the last 7 days [39].
Social participation	The Ability to Participate in Social Roles and Activities scale is an 8-item measure that asks how often an individual has trouble with or has to limit participation in social activities [38].
Process and Mediators/Moderators	
Social needs	Ten questions from the Accountable Health Communities’ Health-Related Social Needs screening tool on the domains of housing, food insecurity, transportation, and utilities will be used to assess unmet social needs [35].
Diabetes knowledge	Diabetes knowledge will be assessed with the Starr County Knowledge Questionnaire
	(DKQ)—a 24-item assessment with a reliability coefficient of 0.78 [40].
Summary of Diabetes Self-Care Activities (SDSCAs)	This scale assesses diabetes self-care activities including general diet, specific diet,
	exercise, blood glucose monitoring, foot care, and smoking [41].
Medication adherence	This will be measured with the 6-item validated self-reported Brooks Medication Adherence Scale (BMAS) [42].
Depression	The Patient Health Questionnaire (PHQ)-9 is a brief questionnaire that scores each of the nine DSM-IV criteria for depression [43].
Anxiety	General anxiety disorder (GAD) will be assessed using the 7-item anxiety scale [44].
Covariates	
Sociodemographics	Previously validated items from the National Health Interview Survey will be used to capture demographic characteristics including age, sex, race/ethnicity, marital status, education, employment, income, and insurance [45].
Health literacy	A 3-item literacy scale noting capacity to obtain, process, and understand basic health-related decisions will measure health literacy [46].
Comorbidities	Previously validated items from the Behavioral Risk Factor Surveillance System will be used to assess the presence of comorbidities [47].

**Table 3 healthcare-12-01991-t003:** Study timeline.

Year	1				2				3			
Quarters	1	2	3	4	1	2	3	4	1	2	3	4
**Start-up Activities**												
Obtain IRB approval												
Register trial on clinicaltrials.gov												
Participant recruitment and enrollment												
30 participants enrolled												
70 participants enrolled												
100 participants enrolled												
Intervention delivery												
Data analysis												
Larger grant submission and final reports												
Manuscripts												

## Data Availability

Data sharing is not applicable. No new data were created or analyzed in this study.
